## Abstract

**Background:**

Head and neck cancers that cause severe aesthetic and functional disorders normally metastasize to the cervical lymph nodes. Patients with cervical lymph node metastasis are undergoing neck dissection. Shoulder complaints are common after neck dissection, with patients reporting symptoms such as pain, weakness, shoulder droop, and disability. However, no safe and effective treatment is available for this condition at present. We will conduct a double-blinded, randomized controlled trial to evaluate the efficacy of carbon dioxide (CO_2_) paste in relieving pain in patients after neck dissection.

**Objective:**

This will be the first clinical study to compare the efficacy of CO_2_ paste with placebo in relieving postoperative pain in patients who underwent neck dissection.

**Methods:**

We will perform this trial at the Kobe University Hospital in Japan. Patients will be randomized 1:1 into the CO_2_ paste and control groups. Patients in the CO_2_ paste group will have the CO_2_ paste applied to the cervical surface skin for 10 minutes once per day for 14 consecutive days. The primary end point of the study is a change in the visual analog scale (VAS) scores of neck pain from baseline on day 1 (preapplication) to the end of drug application (day 15). Secondary end points include changes in the following parameters from baseline on day 1 to the end of drug application (day 15) or the study (day 29): neck pain VAS score (days 1-29), grip strength (days 1-15 and 1-29), VAS scores for subjective symptoms (the feeling of strangulation, numbness, swelling, and warmth in the neck and shoulder region) for days 1-15 and 1-29, whether the VAS score improved more than 30% (days 1-15), the arm abduction test (days 1-15 and 1-29), shoulder range of motion (abduction and flexion) for days 1-15 and 1-29, occurrence of skin disorders, and occurrence of serious side effects. Periodic monitoring will be conducted for participants during the trial. This study was approved by the certified review board of Kobe University.

**Results:**

The intervention commenced in May 2021 and will continue until March 2024. The collected data will provide information on the efficacy of the CO_2_ paste treatment. The primary end point will be compared using the Wilcoxon test, with the 1-sided significance level set at 5%. Each evaluation item will be summarized. Secondary efficacy end points will be analyzed to provide additional insights into the primary analysis. Findings based on the treatment effects are expected to be submitted for publication in 2025.

**Conclusions:**

This trial will provide exploratory evidence of the efficacy and safety of CO_2_ paste in relieving pain in patients after neck dissection.

**Trial Registration:**

Japan Registry of Clinical Trials (jRCT) identifier: jRCTs051210028; https://jrct.niph.go.jp/en-latest-detail/jRCTs051210028

**International Registered Report Identifier (IRRID):**

DERR1-10.2196/50500

## Introduction

Postoperative wound pain in the head and neck region generally improves within 1-2 weeks after surgery. However, patients undergoing cancer treatment often experience continuous, persistent pain, which can cause physical and psychological distress. Surgery and radiation therapy often cause painful scarring and contractures. Musculoskeletal and neuromuscular disabilities after radiotherapy and surgical treatment are major causes of cancer treatment–related side effects. Disabilities in the head and neck region after cancer treatment are related to a patient’s ability to communicate, eat, and work [1]. These changes reduce the functioning and social interaction of these patients [1,2].

Shoulder complaints are common (18%-77%) after neck dissection, even if the spinal accessory nerve has been preserved [3,4]. Symptoms such as pain, weakness, shoulder droop, and disability have been reported in patients after neck dissection [5,6]. Pain is an important factor affecting the quality of life (QOL) of cancer survivors [1,7]. Although various drug treatments are available for preventing or improving the management of chronic postsurgical pain [8-10], these treatments have side effects.

The exact etiology of persistent postsurgical pain remains unclear, but its causes are thought to involve neuropathy [11-13], inflammation [14,15], central sensitization [16,17], and ischemia [18-20]. In rats, decreased blood flow and tissue ischemia cause complex regional pain syndrome–like symptoms [18]. In addition, patients with peripheral arterial diseases experience chronic ischemic pain [20]. Thus, continuous postoperative pain may be reduced by improving the blood flow in the ischemic scar tissue.

We had previously reported the effects of transcutaneous application of carbon dioxide (CO_2_) in a hydrogel as an absorption-promoting agent in healthy individuals and various animal models [21-23]. Transcutaneous application of CO_2_ improves vascularization and exercise performance in rats; it also increases local oxygenation, causing the dissociation of oxygen from hemoglobin (Bohr effect) [23-25]. However, this method uses CO_2_ gas, which is difficult to apply to the head and neck. In a recent study, we investigated the usefulness, safety, and feasibility of a CO_2_ paste by analyzing the changes in blood flow in a phase 1 clinical study in healthy individuals [26]. The CO_2_ paste reacted with water on the skin surface, could infiltrate CO_2_ transcutaneously without the use of external CO_2_ gas, and could be applied to the head and neck region. In the phase 1 clinical study, application of the CO_2_ paste increased the blood flow in the skin and muscles, as observed by dynamic magnetic resonance imaging, and caused no adverse reactions.

This double-blind, randomized controlled trial aims to evaluate the efficacy and safety of CO_2_ paste in decreasing postoperative neck pain in patients undergoing neck dissection.

## Methods

### Objectives

This study will examine whether the application of a CO_2_ paste can reduce postoperative neck pain in patients receiving neck dissection in a double-blinded, randomized controlled trial. The primary objective is to estimate the within-patient differences in visual analog scale (VAS) scores for neck pain ranging from 0 (no pain) to 10 (worst pain) from baseline (day 1: before application) to the end of the study drug application (day 15). The secondary objectives are to evaluate the within-patient differences in the VAS scores for neck pain from baseline (day 1: before application) to the end of study drug application (day 15), grip strength from baseline to the end of the drug application (days 1-15) and the end of the study period (days 1-29), VAS scores for subjective symptoms (the feeling of strangulation, numbness, swelling, and warmth) from baseline to the end of the drug application (days 1-15) and the end of the study (days 1-29), arm abduction [27] from baseline to the end of the drug application (days 1-15) and the end of the study (days 1-29), and shoulder joint range of motion (abduction or flexion) from baseline to the end of the drug application (days 1-15) and the end of the clinical study (days 1-29). In addition, we aim to evaluate whether patients showed a ≥30% improvement in the VAS scores for neck pain from baseline to the end of the drug application (days 1-15) and the end of the study (days 1-29).

### Study Design

This study has been designed as a single-center, placebo-controlled, double-blind, randomized controlled trial. The patient flowchart is shown in Figure 1. This study will be conducted at Kobe University Hospital. All data will be stored and archived at the data center of Kobe University Hospital. We will use Research Electronic Data Capture (REDCap; Vanderbilt University), an electronic data system for clinical research, to manage the data and protect confidentiality before, during, and after the trial. The study population will consist of patients undergoing neck dissection and will be selected based on the inclusion and exclusion criteria listed in Textbox 1. Patients will be recruited from Kobe University Hospital from May 24, 2021, to March 31, 2024. All patients will be asked if they wish to participate in the study and will be enrolled after obtaining written informed consent.

**Figure 1 figure1:**
[figure not shown]
Flowchart of participants. VAS: visual analog scale.

Inclusion and exclusion criteria for the study.
**Inclusion criteria**
Aged 20 years or olderHave complaints of postoperative neck pain after unilateral cervical dissectionBetween 6 months and 3 years after neck dissectionA visual analog scale score of 1 or higher for neck painHave given voluntary consent to participate in this clinical study
**Exclusion criteria**
Hypersensitivity to drugs, including severe allergiesPeripheral arterial disease, ischemia (Fontaine III-IV), and ischemic cerebral artery diseaseHeart failure (New York Heart Association IV) and ischemic heart disease (Canadian Cardiovascular Society functional classification 3-4)Female patients who are pregnant, lactating, wishing to become pregnant during the study period, or are fertile and cannot accept an effective contraceptive methodSevere respiratory disease with oxygen saturation (SpO2) less than 90% at restSkin ulcers larger than 4 cm × 4 cm × 1 cm or skin diseases making it difficult to apply the pasteDeemed inappropriate for participation in this clinical study by the investigators

### Randomization (Allocation)

Using the permutation random block method stratified by category, participants will be randomly assigned to either the CO_2_ paste group or the placebo control group at a 1:1 allocation ratio. To ensure that blinding is maintained, the block size will not be disclosed. The allocation sequence for the randomization method will be generated by a biostatistician. All participants who provide consent to participate, fulfill the inclusion criteria, and do not meet any of the exclusion criteria will be randomized. The eligibility of each participant will be confirmed. A subject-enrollment confirmation form containing the eligibility judgment, randomization assignment results from the generated random sequence, and the enrollment number will be issued.

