### Statistical Analysis

The primary objective of this clinical study was to evaluate the efficacy of the CO_2_ paste versus the placebo in terms of the change in VAS scores for neck pain (the primary end point). For the comparison of the primary end point, the Wilcoxon test will be performed for the null hypothesis, “There is no difference in the change in VAS values for neck pain at day 15 between the placebo group and the CO_2_ paste group.” The significance level will be set at 5.0% (1-sided). Each evaluation item will be summarized. Secondary efficacy end points will be analyzed to provide additional insights into the primary analysis. No adjustment for multiplicity will be made in the analyses of the secondary efficacy end points. The significance level for hypothesis testing is 5% (2-sided) with 2-sided 95% CIs. The incidence and rate of disease will also be evaluated. The safety end point is the frequency of the occurrence of adverse reactions. Tables will be prepared for the end points, and exact 2-sided 95% CIs of the binomial distribution will be calculated for each group to estimate the proportions.

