### Sample Size Calculation

Most patients are expected to have a baseline VAS score of 2-3 cm. For the primary end point (the amount of change in VAS values for neck pain), we estimated that the mean difference in change between the CO_2_ paste application and placebo groups would be 2 (SD 1.5) cm. A Wilcoxon test (a nonparametric test) will be performed considering the possibility that participants with a baseline score of less than 2 cm might be enrolled. The number of cases based on the Wilcoxon test can be calculated by multiplying the number of cases based on the *t* test [28]. Although the constant for multiplication is 1.045 in the case of a normal distribution, since the participants in this study were not assumed to be normally distributed, the number of cases was calculated by multiplying by 1.2. When conducting a *t* test with a 1-sided significance level of 5.0% and a power of 80%, a total of 7 participants were required per group. When the number of cases was multiplied by 1.2, the total number of cases was 8.4. Therefore, considering drop out cases, 20 cases would be sufficient to maintain power.

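### Allocation is stratified but the primary Wilcoxon test as stated is not, so the test is conservative and gives up some power if the stratum is moderately prognostic

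*Protocol article*

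**What the plan says.** Under Randomization (Allocation), the protocol article states: "Using the permutation random block method stratified by category, participants will be randomly assigned", in a 1:1 ratio. It does not say what the category is or how many levels it has. The block size is withheld on purpose: "To ensure that blinding is maintained, the block size will not be disclosed".

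Under Statistical Analysis: "For the comparison of the primary end point, the Wilcoxon test will be performed for the null hypothesis". That hypothesis is no difference between the two groups in VAS change at day 15, tested at a one-sided 5% level. The Results part of the Abstract names the same test. Neither place mentions strata, a stratified version of the test or an adjustment.

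Under Sample Size Calculation, the trial is sized as an ordinary two-sample comparison with a "mean difference in change between the CO_2_ paste application and placebo groups would be 2 (SD 1.5) cm". A t-test number is multiplied by 1.2 for the Wilcoxon test, and the final total is 20 patients.

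**The concern.** Stratified blocks keep the arms nearly balanced on the stratum. If the stratum predicts pain change, the true chance variation of the group comparison is smaller than under unrestricted allocation. The plain Wilcoxon test counts every 10:10 split of the 20 patients as equally likely, including splits unbalanced on the stratum that the design rules out or makes rare. Its reference distribution is then too wide and the p-value tends to be too large.

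At stake is efficiency in a trial of about 10 per arm with one primary test. The test would run below its nominal level, and part of the precision that stratification provides would go unused. A choice between a plain and a stratified test that is left open until the data are unblinded would also allow selection between two p-values.

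**Working it through.** **1. The plan's own sample size.** Inputs from Sample Size Calculation: difference 2 cm, SD 1.5 cm, one-sided 5%, power 80%.

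n per arm = 2 × (1.645 + 0.842)² × (1.5/2)² = 2 × 6.18 × 0.5625 = 6.96, so 7. Then 7 × 1.2 = 8.4, or 9 per arm and 18 in total; 20 leaves 2 patients for dropout (10%). The stated 7, 8.4 and 20 are reproduced. An exact noncentral t calculation gives 76.0% power at 7 per arm and 81.3% at 8, a difference of one patient per arm. The calculation has no term for strata.

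**2. Assumptions needed.** The document does not give the factor, the number of strata or how well the factor predicts change. I assume 20 evaluable patients, 10 per arm, normal data and exact balance within strata. The prognostic strength is varied as R², the share of outcome variance explained by the stratum. For two equal strata with means d apart, R² = (d/2)² / 1.5², so d = 2 × 1.5 × √R². R² of 0.05, 0.10, 0.25 and 0.40 correspond to d of about 0.67, 0.95, 1.50 and 1.90 cm.

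**3. Two strata of 10 (5:5), total SD 1.5 cm.** Exact one-sided plain Wilcoxon against exact stratified (van Elteren type) Wilcoxon, by simulation with 100,000 runs per cell. Because ranks are discrete, the highest attainable level below 5% is about 4.5% for both tests.

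| R² | Error, plain | Error, stratified | Power at 2 cm, plain | Power at 2 cm, stratified |
|---|---|---|---|---|
| 0 | 4.6% | 4.6% | 85.8% | 84.1% |
| 0.05 | 4.1% | 4.5% | 86.2% | 85.9% |
| 0.10 | 3.6% | 4.4% | 86.6% | 87.3% |
| 0.25 | 2.5% | 4.6% | 87.8% | 91.9% |
| 0.40 | 1.3% | 4.4% | 89.2% | 96.2% |

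Power forgone by the plain test is about 1 point at R² 0.10, 4 at 0.25 and 7 at 0.40. At R² 0.05 there is nothing to gain, and at R² 0 the stratified test loses about 1.7 points.

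**4. If 1.5 cm is the within-stratum SD.** The total SD is then larger, and plain against stratified power at 2 cm becomes 83.4% vs 84.2% (R² 0.10), 79.8% vs 84.1% (0.20), 77.3% vs 84.1% (0.25) and 68.0% vs 84.3% (0.40). The plain test drops below 80% from R² of about 0.20.

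**5. Five strata of 4 (2:2), total SD 1.5 cm.** Plain against stratified power at 2 cm is 85.7% vs 71.1% (R² 0), 86.6% vs 75.6% (0.10), 88.2% vs 82.5% (0.25) and 89.6% vs 89.4% (0.40). The exact stratified test can attain only 2.7% here, which contributes to the loss. The plain test is still conservative (3.6% at R² 0.10, 2.5% at 0.25), but the van Elteren test is not the remedy.

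**The case against.** The strongest reply is that the document does not say the strata will be ignored. The van Elteren test is itself a Wilcoxon-type test, this is a condensed article, and the analysis plan, which is not shown, may specify a stratified version. That is fair as far as it goes. But the article does more than omit a detail: it names the primary test, gives it a two-group null hypothesis and sizes the trial on an unstratified comparison. Read as written, the test does not match the allocation.

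Several stronger readings are tempting, and the documents do not support them.

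- *The false-positive rate is inflated.* It is not; the departure is towards conservatism.
- *The trial is underpowered.* With 1.5 cm as the total SD, which is how Sample Size Calculation reads, and all 20 patients evaluable, plain-test power at 2 cm is about 86% or more in every case examined. A shortfall below 80% needs 1.5 cm to be the within-stratum SD and R² of about 0.20 or more.
- *Power is lost whenever the stratum predicts change.* A weak stratum gives no gain, and with many small strata the stratified rank test is worse.
- *The benefit of stratifying is thrown away.* At a fixed total SD, plain-test power rises from 85.8% to 89.2% as R² goes from 0 to 0.40, so balance still helps. Only part of the benefit is unused.

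It can also be said that nothing in the document shows the factor to be prognostic. That stands. R² of 0.25 means strata 1.5 cm apart in mean change, which is large when most baseline scores are expected to be 2 to 3 cm. The lower part of the range is at least as plausible.

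**Conclusion.** The mismatch between stratified allocation and the unstratified primary test stands, and so does its direction. Its size is modest and conditional. With two equal strata, total SD 1.5 cm and 20 evaluable patients, a moderately prognostic factor brings the actual one-sided error to about 3.6% (R² 0.10) or 2.5% (R² 0.25) and costs about 1 or 4 points of power at 2 cm. Since the factor, the number of strata and the prognostic strength are not given, this is an assumed range and not an estimate for this trial. A positive result from the plain test would remain valid on this count; the cost is a somewhat greater chance of missing a real effect.

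**What to change.** Before unblinding, state the stratification factor and its number of levels in the analysis plan, and make the primary analysis follow it.

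- With only two or so strata: a van Elteren (stratified Wilcoxon) test using the randomisation strata.
- With several small strata: an aligned-rank or linear model with stratum as a factor, or a re-randomisation test within strata. The van Elteren test should not be used here, as it can lose more than 10 points of power.
- In either case, keep the plain Wilcoxon test as a sensitivity analysis.

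The cost is wording in the Statistical Analysis section and the analysis plan; no patients or visits are added. With two strata that turn out not to be prognostic, the stratified test gives up about 1 to 2 points of power.

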### Experimental Drugs

The CO_2_ paste (direCO_2_t) is manufactured as an experimental drug at the CO2TECH, a limited liability company. The CO_2_ paste contains 1,3-butylene glycol and other components, including sodium hydrogen carbonate, malic acid, sodium dihydrogen phosphate, an alkyl-modified carboxyvinyl polymer, and carboxyvinyl polymer. The placebo paste is a formulation in which the sodium bicarbonate in the CO_2_ paste is replaced by a nonreactive material (sodium chloride).

### Treatment and Assessment Schedule

Within 4 weeks of enrollment, the VAS score for neck pain will be evaluated 1 week before the administration of the experimental drug during the preobservation period. On the first day of treatment, body temperature, blood pressure, oxygen saturation, and pulse rate will be measured by a physician, dentist, or nurse before and after the application of the experimental drug. The paste will be applied at 0.2 g-0.3 g/100 cm^2^ to the affected neck area once per day for 14 consecutive days. The duration of each application will be 10 minutes, and the paste will be wiped off after application.

### Data Collection

The data collection schedules are presented in Table 1. The primary investigator or subinvestigator will enter the case report form (CRF) data for each participant into the electronic data capture (EDC) system. The principal investigator will confirm that the entered CRF data are complete and correct, electronically sign the CRF on the EDC system, and print out the signed CRF for filing. The CRF printout will be retained. If any queries about the CRF data are entered by the staff at the data center, the primary investigator or subinvestigator will be required to promptly respond to them.

**Table 1 table1:** Data collection schedule.

	Registration (within 4 weeks before allocation)	Preobservation (7±3 days before allocation)	Allocation day 1 (preapplication)	Allocation day 1 (postapplication)	Postallocation day 15+1 (finish application)	Postallocation day 29+3	Exclusion	Within 7 days after exclusion
Assessment of eligibility criteria	✓							
Obtain consent	✓							
Registration	✓							
Patient characteristics^a^	✓							
Allocation and start of the application			✓					
VAS^b^ of neck pain		✓	✓	✓	✓	✓		
VAS values of subjective symptoms^c^			✓	✓	✓	✓		
Strength of grip arm abduction test^d^ Shoulder joint range of motion (abduction or flexion)			✓		✓	✓		
Adverse events				✓	✓	✓	✓	✓
Vital sign^e^	✓		✓	✓	✓		✓	✓
Oxygen saturation (SpO_2_)	✓		✓				✓	✓
Confirmation of days of application					✓		✓	

^a^Sex, date of birth, age, medical history, comorbidity, primary disease, TNM classification, the number of days after surgery, the range of neck dissection, preservation of sternocleidomastoid muscle, accessory nerve, and internal jugular vein, and the details of adjuvant therapy.

^b^VAS: visual analog scale.

^c^Strangulation, numbness, swelling, and warmth.

^d^Arm abduction test: up to 180˚ without pain or effort (5 points), up to 180˚ but with pain or effort (4 points), up to more than 150˚ but less than 180˚ (3 points), up to more than 90˚ but not less than 150˚ (2 points), up to approximately 90˚ (1 point), and up to less than 90˚ (0 point) [27].

^e^Body temperature, blood pressure, and pulse rate.

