### Main Outcomes

The primary end point for efficacy is the change in the VAS score for neck pain from baseline (day 1: before application) to the end of the study drug application (day 15).

The secondary efficacy end points are as follows:

Change in the VAS score for neck pain from baseline (day 1: before application) to the end of the clinical study (day 29).Changes in grip strength from baseline to the end of the drug application (days 1-15) and the end of the study (days 1-29).Changes in VAS scores for subjective symptoms (feeling of strangulation, numbness, swelling, and warmth) from baseline to the end of the drug application (days 1-15) and the end of the study (days 1-29).Whether the VAS score for neck pain showed a ≥30% improvement from baseline to the end of the drug application (days 1-15) and the end of the study (days 1-29).Change in arm abduction [27] from baseline to the end of drug administration (days 1-15) and the end of the study (days 1-29).Change in shoulder joint range of motion (abduction and flexion) from baseline to the end of drug application (days 1-15) and the end of the study (days 1-29).

The secondary end point for safety is the presence or absence of adverse events such as skin disorders and serious diseases. The relationships among the interventions, outcomes, other assessments, and visits associated with the participants in this study are shown in Table 1.

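### Table 1 footnote d misstates the limit of the 2-point class of the arm abduction test, so the printed scale has a gap below 150° and an overlap above it

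*Protocol article*

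**What the plan says.** Footnote d of Table 1 (Data Collection) sets out a six-level score for the arm abduction test, from best to worst:

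- 5: "up to 180˚ without pain or effort (5 points"
- 4: "up to 180˚ but with pain or effort (4 points"
- 3: "up to more than 150˚ but less than 180˚ (3 points"
- 2: "up to more than 90˚ but not less than 150˚ (2 points"
- 1: "up to approximately 90˚ (1 point"
- 0: "up to less than 90˚ (0 point"

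Main Outcomes lists the score among the secondary efficacy end points: "Change in arm abduction [27] from baseline to the end of drug administration (days 1-15) and the end of the study (days 1-29". Table 1 schedules the test on day 1 before application, at day 15 and at day 29. The Objectives and Main Outcomes sections cite a reference for the scale but do not restate its classes, so footnote d is the only definition in the article.

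**The concern.** A scoring rule should put every possible angle in exactly one class. The 2-point class as printed does not allow this. Its second condition, at least 150°, is stricter than its first, above 90°, so the class reduces to 150° and above. It then leaves the middle of the scale empty and lies on top of the 3-, 4- and 5-point classes.

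The end point is a change score measured at three visits. If an assessor followed the printed words, or resolved them differently at different visits, a one-point change could appear or disappear without any change in the patient. The article prints this rule in full, so this is not a detail left to another document, and no other section corrects it.

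**Working it through.** **Inputs.** The six class definitions in footnote d, with x as the abduction angle in degrees. One assumption is needed: *approximately 90°* is taken as exactly 90°. A looser reading would absorb a few degrees on either side, but not the range up to 150°.

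**Step 1: the 2-point class as printed.** The conditions are x > 90 and not (x < 150). The second is x ≥ 150, which already implies the first. The class is therefore x ≥ 150.

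**Step 2: classify every whole degree from 0 to 180 as printed.**

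| Angle | Whole-degree values | Classes met |
|---|---|---|
| 0° to 89° | 90 | 0 |
| 90° | 1 | 1 |
| 91° to 149° | 59 | none |
| 150° | 1 | 2 |
| 151° to 179° | 29 | 2 and 3 |
| 180° | 1 | 2, together with 4 or 5 |

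The values add up: 90 + 1 + 59 + 1 + 29 + 1 = 181. Of these, 59 have no class and 29 + 1 = 30 have more than one. Exactly 150° is not doubly scored, because the 3-point class begins above 150°.

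**Step 3: repeat with 150° as an upper limit.** The limit can include 150° or exclude it.

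| Limits of the 2-point class | Values without a class | Values with more than one class |
|---|---|---|
| above 90°, not more than 150° | 0 | 0 |
| above 90°, less than 150° | 1 (exactly 150°) | 0 |

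With 150° included, the counts are 90 (score 0), 1 (score 1), 60 (score 2), 29 (score 3) and 1 (score 4 or 5), again 181 in total. At 180°, pain or effort separates 4 from 5. Changing *less* to *more* is therefore enough to repair the scale. Excluding 150° moves the defect to a single angle.

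**The case against.** The strongest reply is that nobody would be misled. The footnote steps down from 180° to below 90°, and a lower limit of 90° in the 2-point class has a purpose only if 150° is the upper limit. An assessor is unlikely to leave 120° unscored or to give 165° two points. This stands, and it limits the practical effect. It does not make the printed rule correct.

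A reader might go further and infer that assessors could not score the middle range, that scores already entered are wrong, and that they should be recalculated from the shoulder range of motion. The documents do not support this, for three reasons.

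- The article condenses protocol version 3.0. The CRF and the assessor instructions are not shown, and nothing indicates that they carry the same wording.
- Range of motion cannot stand in for the score. Scores 5 and 4 differ only by pain or effort at 180°, which an angle does not record. Table 1 joins abduction and flexion with *or* while Main Outcomes joins them with *and*, so an abduction angle at every visit is not clearly assured. The article also does not say that the two tests are done under the same conditions.
- It might be argued that these patients typically have limited abduction, so that most would fall in the unscored range. The Introduction names pain, weakness, shoulder droop and disability. Eligibility rests on neck pain with a visual analog scale score of at least 1. Neither establishes where on the abduction scale the patients lie.

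The stakes are also modest. Secondary end points support the primary analysis and carry no multiplicity adjustment, and shoulder range of motion is a separate end point.

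**Conclusion.** The 2-point class is wrong as written. Read literally, angles above about 90° and below 150° have no score, angles above 150° and below 180° have two, and 180° meets the 2-point class in addition to 4 or 5. These counts rest only on the printed definitions and on taking the 1-point class as exactly 90°.

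It is most likely a slip of *less* for *more*, in the definition of one secondary end point. The primary end point, the sample size and the safety assessment do not depend on it. As a scale of possible effect: if the 20 planned cases mean 10 per arm, one patient misplaced by one point would move an arm mean by 1/10 = 0.1 point on the 0 to 5 scale. This is hypothetical, because the documents show no misplaced score. The point is a minor but definite correction.

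**What to change.** In footnote d, redefine the 2-point class as more than 90° but not more than 150°. Avoid *less than 150°*, which would leave exactly 150° without a score. Check the corrected wording, including where 150° itself belongs, against the cited scale, the full protocol and the CRF.

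If the CRF and the full protocol already have the right wording, only the article needs correcting, at the cost of one phrase. If the CRF carries the same error, correct it and query discrepant scores of 2 or 3 with the assessors before unblinding. Recorded shoulder abduction angles, where available, can flag scores for query but should not overwrite them. With about 20 patients and three visits, there are about 60 scores to look through (20 × 3).
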